#### Additional outcomes

SEMG is widely used in the field of clinical neurophysiology and can be used not only for functional diagnosis, but also for monitoring treatment results. Currently, orthopedic injury is one of the most prominent application fields [48–50]. Before sEMG signal acquisition, participants will be told to wear loose trousers to expose the thighs at a room temperature of approximately 25 °C. To ensure the quality of the EMG signals collected, the evaluator should shave the hair from the leg area where the electrode is attached and disinfect it with 75% alcohol before attaching the electrode. The placement requirements for disposable ECG electrodes (Ag/Cl, T-800) include (1) the central distance of the bipolar electrode is 2 cm; (2) the central connection of the bipolar electrode is parallel to the long axis of the muscle fibers below it; and (3) the bipolar electrode should be attached to the ventral portion of the medial vastus muscle, rectus femoris muscle, and lateral vastus muscle. The belly of the rectus femoris is located at the midpoint of the line between the anterior superior iliac spine and the superior edge of the patella, and the belly of the lateral femoral muscle is located at the midpoint between the greater trochanter and the inferior edge of the patella. Because preoperative and postoperative pain leads to an inhibitory protective reflex of the medial vastus muscle and disuse atrophy of some muscle fibers, it is difficult to identify the belly of the medial vastus muscle quickly and accurately. The evaluator will place a towel roll under the healthy popliteal fossa and ask the participant to press the towel roll into the bed as forcefully as possible to straighten the knee joint. At this point, there is a visible protuberant area above the medial patella, that is, the belly of the medial vastus muscle on the operative side relative to the healthy side; thus, the specific position of the belly of the medial vastus muscle on the operative side can be determined; (4) the reference electrode will be placed at the fibular head. The sEMG signals of the quadriceps femoris will be measured and recorded using the TeleMyo 2400 wired sEMG tester (NORAXON USA Inc., Scottsdale, AZ, USA) at a sampling frequency of 1500 Hz. Channel 1 connects with the right lateral vastus muscle, channel 2 connects with the left medial vastus muscle, channel 3 connects with the right rectus femoris muscle, channel 4 connects with the left rectus femoris muscle, channel 5 connects with the right medial vastus muscle, and channel 6 connects with the left lateral vastus muscle. To reduce the interference to the EMG signal caused by the small movement between the metal chuck and the electrode piece of the EMG acquisition line, disposable medical rubber paste will be used to fix the EMG acquisition line metal chuck and the electrode piece. If it is too tight, fixation will be poor; therefore, the fixed tightness of the plaster is adjusted with the minimum influence on the zero EMG value as a reference. Simultaneously, under the premise of not affecting the exercise mode, the EMG acquisition line should be fixed to prevent pulling in the processes of sitting and standing up.

When conventional analgesia programs cannot effectively improve pain, additional analgesics will comprise intramuscular injection of 40 mg parecoxib sodium (Pfizer Pharmaceutical Co., Ltd., national drug standard: J20130044). The frequency and time of use will be recorded.

Furthermore, to study the effect of emotional state on brain activity, the SAS and SDS will be applied. The SAS and SDS have high validity and objectivity in clinical research; they are often used not only to screen for depression, but also as indicators of severity and measurement of outcome. For example, in the study of chronic pain management, they are used as one of the observation indicators [51]. Patient emotional state is evaluated by scoring 20 related items in each of the two scales [52, 53].

### Data management and monitoring

Clinical data will be carefully preserved using paper and electronic case report forms. It is stipulated that only result evaluators have access to case report forms, and they will check the data entered to ensure no duplication. In the course of the trial, Shanghai Guanghua Integrated Traditional Chinese and Western Medicine Hospital will conduct regular reviews, and the hospital ethics committee will supervise every week to avoid violations. The final experimental dataset will not be accessible to anyone except specialized data statisticians, and the dataset will contain only encoded data and will not contain participant information. The relevant research team will monitor the safety, progress, research integrity, and design aspects at several meetings. The Finance Section of the Shanghai Guanghua Integrated Traditional Chinese and Western Medicine Hospital will audit the costs of this study.

### Adverse events of EA

The main EA-related complications include dizziness, acupuncture stagnation, acupoint hematoma, pain > 2 h after continuous acupuncture, and bleeding. Any such adverse events during the trial will be recorded.

### Blinding assessment

To evaluate blinding, we will use a questionnaire completed within 5 min of the final intervention. The percentage of participants from each group who believed they had received real EA treatment will be recorded. The difference in the success rate of blinding among the participants will be determined.

### Statistical analysis

Based on the intention-to-treat principle, a full analysis set and per-protocol sets will be used for the primary analysis. Sensitivity analysis will be performed to determine the impact of incomplete records on the results. Missing data will not be imputed. For the clinical data, statistical analyses will be performed using the statistical package IBM SPSS Statistics V21 (IBM Corp., Armonk, NY, USA). Complete follow-up assessments of the participants will be performed using the per-protocol and intention-to-treat populations. The statistical analysis will include four aspects. First, for the measured data with normal and non-normal distributions, the mean ± SD and median will be used to describe the concentration trend and dispersion degree, respectively. Two independent sample *t*-tests and Mann-Whitney *U* tests will be used to compare the differences between groups. Second, the quadruple chi-squared test will be used to evaluate the sex composition ratio (which is a classified variable). Third, the Mann-Whitney *U* test will be used to compare the differences between the groups in the ranked data. Finally, a generalized linear mixed model will be used to compare the repeated measurement data. The statistical significance will be set to two-sided *p* < 0.05.

The fMRI scan data will be preprocessed and analyzed using SPM12 software (http://www.fil.ion.ucl.ac.uk/spm/) performed on MATLAB 2015b (MathWorks, Inc., Natick, MA, USA). The main preprocessing steps are as follows: (1) remove the functional image data of the first 10 time points while waiting for the imaging gradient to reach a stable state; (2) carry out time correction, remove the time difference between different layers by correction, and then perform head correction; (3) match the functional image to the corresponding anatomical image and convert it to a standard Montreal Neurological Institute space—the resampling size of the image data pixels is 3 × 3 × 3 mm^3^; (4) use the linear regression method to remove the related variables, including the average signal of the cerebrospinal fluid and 12 cephalic parameters; and (5) process the data by removing high-frequency noise and low-frequency drift. The data are mainly processed by linear drift and band-pass filtering (0.01–0.08 Hz). After data preprocessing, the amplitude of low-frequency fluctuation, regional homogeneity, and functional connectivity will be used to investigate the cerebral responses of the different study groups. A two-sample *t*-test will be used to evaluate intra- and inter-group differences to analyze possible brain responses, and a correlation analysis will be conducted to investigate the changes in fMRI image data and the corresponding clinical data in each group.

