**Methods:**

This is a randomized sham-controlled single-blind clinical trial. Patients will be allocated randomly to two parallel groups (A: opposing electroacupuncture group; B: sham opposing electroacupuncture group). The Yinlingquan (SP9), Yanglingquan (GB34), Futu (ST32), and Zusanli (ST36) acupoints will be used as the opposing needling sites in both groups. In group A, the healthy lower limbs will receive electroacupuncture, while in group B, the healthy lower limbs will receive sham electroacupuncture. At 72 h after unilateral TKA, patients in both groups will begin treatment once per day for 3 days. Functional magnetic resonance imaging will be performed on all patients before the intervention, after unilateral TKA, and at the end of the intervention to detect changes in brain activity. Changes in pressure pain thresholds will be used as the main outcome for the improvement of knee joint pain. Secondary outcome indicators will include the visual analogue scale (including pain during rest and activity) and a 4-m walking test. Surface electromyography, additional analgesia use, the self-rating anxiety scale, and the self-rating depression scale will be used as additional outcome indices.

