### Outcome evaluations

The clinical evaluations will measure knee pain and physical function. The primary outcome measure will consist of the pressure pain thresholds (PPTs), and the secondary outcome indicators will include the visual analogue scale (VAS), including pain during rest and activity, and the 4-m walking test (4MWT). Additional outcome indicators will comprise surface electromyography (sEMG), the self-rating anxiety scale (SAS), the self-rating depression scale (SDS), and the use of additional analgesics. Data regarding PPTs, VAS, and the 4MWT will be collected at baseline, 30 min before each acupuncture treatment, and immediately after each acupuncture treatment. sEMG, SAS, and SDS data will be collected at baseline, before the first acupuncture session after the operation, and after all interventions have been completed. The use of additional analgesics will be assessed at the end of the intervention period.

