#### Primary outcome

PPTs are quantitative sensory tests that are widely used in the prediction and evaluation of clinical therapeutic effects in patients with KOA [40–43]. An experienced trained clinician ([name]) will perform all PPT measurements using the FDX-50 portable pain tester (Wagner Instruments, Greenwich, CT, USA) to minimize measurement variability. The specific operation is as follows: the patient will lie down in the supine position, and two points of the operated knee joint will be used for testing: (1) lateral point: located 3 cm lateral to the midpoint of the lateral edge of the patella, and (2) medial point: located 3 cm medial to the midpoint of the medial edge of the patella. A 1-cm^2^ probe will be applied perpendicular to the skin, and the pressure will be maintained at 10 kPa/s. Patients will be instructed to say “stop” the first time they feel pain, at which point the PPT readings will be recorded. Three readings will be taken at each site, with the final two readings averaged to increase the reliability. There will be a small change in the probe position of the pain meter on the skin between each reading to avoid sensitization of the test area [44].

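### The primary outcome, pressure pain threshold (PPT), has two knee sites, seven measurement times, competing tests and two analysis sets, but no single primary contrast and no fixed reference for change

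*Protocol article*

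**What the plan says.** All references are to the Protocol article.

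- **Outcome.** The Methods paragraph of the Abstract states: "Changes in pressure pain thresholds will be used as the main outcome for the improvement of knee joint pain". Outcome evaluations names PPTs as the primary measure, with no time point or summary.
- **Sites.** Primary outcome: "two points of the operated knee joint will be used for testing", one lateral and one medial. The last two of three readings are averaged within each point. No rule combines or ranks the two points.
- **Times.** Outcome evaluations: "Data regarding PPTs, VAS, and the 4MWT will be collected at baseline, 30 min before each acupuncture treatment, and immediately after each acupuncture treatment". There are three daily sessions.
- **References for change.** Study design and participants puts the baseline assessment on the day before the operation. The reading before session 1 comes after surgery, because treatment starts 72 hours after the knee replacement.
- **Tests.** Statistical analysis: "Two independent sample *t*-tests and Mann-Whitney *U* tests will be used to compare the differences between groups", then "a generalized linear mixed model will be used to compare the repeated measurement data". No covariate is mentioned for either.
- **Error rate and sets.** "The statistical significance will be set to two-sided *p* < 0.05". The same section uses the full analysis set and the per-protocol sets for the primary analysis. It gives no multiplicity rule.

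**The concern.** Choosing the site, time and summary that make up the primary result belongs in the protocol. This article describes PPT measurement down to probe area and the averaging of readings, but does not reduce the readings to one primary variable. Several PPT results could each be reported as the primary one, and a finding significant at 5% could not be read at that level.

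The reference for change matters as well. Change from the pre-operative value mixes the effect of surgery on the knee with the effect of treatment. Change from the value before session 1 does not. The second value describes the acutely painful knee just before treatment starts, so it is the natural adjustment variable, yet no stated method uses it as a covariate.

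**Working it through.** **The plan's own figures.** The only error-rate figure is two-sided 0.05. The planned 40 per group comes from imaging considerations. The article gives no PPT standard deviation (SD), effect size, correlation or power, so there is no PPT calculation to reproduce.

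**Inputs from the article.** Sites: 2. Times: 1 baseline + 3 pre-session + 3 post-session = 7. Times after the first session: 3 post-session + 2 pre-session (sessions 2 and 3) = 5. Patients per group after the stated 20% drop-out: 40 × (1 − 0.20) = 32.

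**Assumed inputs.** Correlation between PPT tests 0.5, 0.7 or 0.9, equal for all pairs; correlation of pre-session-1 with final PPT 0.5 or 0.7; true difference 0.6 SD.

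**Chance of at least one false positive.** Under independence it is 1 − 0.95^k for k tests. Under correlation it was simulated with two-sample t-tests, 32 per group, no true difference.

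| Candidate primary results | k | Independent | Correlation 0.5 | 0.7 | 0.9 |
|---|---|---|---|---|---|
| 2 sites, one time | 2 | 9.8% | 9% | 8% | 7% |
| 2 sites × 3 post-session times | 6 | 26.5% | 21% | 16% | 11% |
| 2 sites × 5 times after session 1 | 10 | 40.1% | 29% | 22% | 13% |

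These rows count sites and times only. Two analysis sets and two families of method add further routes, not quantified here. Reporting whichever of the t-test and Mann-Whitney test is smaller, on one normal outcome with 40 per group, gave 5.5% in 4,000 runs, so that choice contributes little.

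**How to use the value before session 1.** With equal SDs and pre-post correlation r, the standardised difference is 0.6/√(2(1 − r)) for a change score and 0.6/√(1 − r²) for analysis of covariance (ANCOVA). Power is for 32 per group at two-sided 0.05.

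- r = 0.5: change score 0.6/1 = 0.60, power 66%; ANCOVA 0.6/0.866 = 0.69, power 78%.
- r = 0.7: change score 0.6/0.775 = 0.77, power 86%; ANCOVA 0.6/0.714 = 0.84, power 91%.

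ANCOVA is the more powerful of the two at both correlations.

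**The case against.** A reader might infer from the t-test sentence that the primary PPT comparison is an unadjusted t-test or Mann-Whitney test and that the pre-treatment PPT goes unused. The article does not support that. The sentence covers measured data in general and does not name PPT. The same section gives repeated measurements a mixed model, and PPT is repeated. The Abstract defines the outcome as change, so some earlier value enters, and a mixed model on all readings could also use the pre-treatment ones. A power comparison against an unadjusted final-value t-test would therefore use a comparator the plan does not fix.

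Other points also stand. The t-test and Mann-Whitney test read as alternatives chosen by distribution. The 40% needs ten independent tests, which repeated readings on one knee are not, and counts pre-session times that few would propose as primary. The objectives concern brain activity, and the sample size rests on imaging. Model terms may be set out in an analysis plan that is not shown.

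These arguments narrow the point without removing it. PPT is the declared primary outcome. The article itself names two methods and two sets for it without ranking them, leaves two sites uncombined, and does not say where change starts. Even two sites at a single time take the rate above 5% if either may count.

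**Conclusion.** The point holds as an incompletely fixed primary contrast. The plan leaves primary site, time, method, analysis set and reference for change open, and tests each result at 0.05. If any site or time may count as success, the false-positive chance is about 7-10% for two sites at one time, 11-26% across three post-session times, and 13% to an upper bound of 40% across five times. These figures rest on assumed equal correlations, with independence as the extreme. They apply only if success may be claimed on any one result. The power figures also rest on an assumed 0.6 SD effect and assumed correlations, and serve only to choose between ANCOVA and a change score.

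**What to change.** Name one primary contrast: the mean of medial and lateral PPT immediately after session 3, compared between groups in the full analysis set. This time matches the second MRI scan, which follows the last intervention. Analyse it by ANCOVA, or by the already planned mixed model with that contrast specified, with the PPT taken 30 minutes before session 1 as covariate. Make single sites, other times, the t-test and Mann-Whitney comparisons and the per-protocol set secondary.

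One contrast keeps the test at 0.05. If the sponsor prefers to keep several primary results, a Bonferroni level would be 0.05/2 = 0.025 for two sites at one time, or 0.05/6 = 0.0083 for two sites at three post-session times.

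The cost is analysis wording only, since every value is already collected. The downside is that single-site and single-time results lose primary status. The change should be dated and made before unblinding.

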### Objectives

The current study protocol aims to (1) investigate the influence of opposing EA treatment on the brain activities of patients after unilateral TKA compared with that of sham opposing EA treatment and (2) analyze the possible correlations between the changes in cerebral activity and the improvement of clinical variables in each group, exploring how opposing EA modulates brain function to manage acute pain after TKA.

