### Sample size

The sample size estimation for neuroimaging is different from that of classical randomized controlled trials. Compared with the evaluation of curative effect, neuroimaging studies focus more on mechanisms of the effects. Previous literature indicates that, for MRI studies, 12–15 participants in each group are sufficient [37, 38]. To obtain stable results of brain functional network analysis, the current study design requires at least 20 participants in each group. However, considering a 20% drop-out rate during the trial and the possibility of head movement artifact during the MRI scan that may render the images useless, we plan to recruit 80 participants (40 patients per group). Each group will undergo two MRI scans to investigate the different central responses between contralateral acupuncture and sham acupuncture after right TKA.

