### MRI data acquisition

The functional MRI (fMRI) data will be acquired by a clinical 1.5-T whole-body MRI scanner (United Imaging, Shanghai, China) at the MRI Center in Guanghua Hospital, Shanghai University of Traditional Chinese Medicine. The participants will be asked to wear soundproof earplugs during the scan, and the examiner at the MRI center will add a sponge between the patient’s head and the head coil to reduce noise and to discourage patient head movement. The participants will be instructed to stay awake and relaxed and to close their eyes during the scan and not think of anything in particular. Each patient will undergo two MRI scans; the first scan will be performed before the first intervention after surgery, and the second after all interventions are completed. After each scan, participants will complete a simple questionnaire to determine if they fell asleep during the scan.

Resting-state fMRI (rs-fMRI) images will be generated using a rapid-gradient echo-planar imaging sequence with the following settings: repetition time, 3,000 ms; echo time, 30 ms; flip angle, 90°; field of view, 225 × 225 mm^2^; acquisition matrix, 64 × 64; 43 slices; slice thickness 3.5 mm; voxel size, 3.52 × 3.52 × 3.52 mm^3^; and bandwidth, 2250 Hz/pixel. Each scan will require 12 min 13 s. Three-dimensional T1-weighted magnetization-prepared rapid-gradient echo sagittal images will be captured using the following parameters: repetition time, 10.4 ms; echo time, 4.4 ms; inversion time, 750 ms; flip angle, 10°; matrix, 256 × 232; slice thickness, 1 mm; and voxel size, 1 × 1 × 1 mm^3^. Each scan will require 3 min 32 s.

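### The opposing EA versus sham comparison of brain activity is assigned a two-sample t-test with no baseline covariate, which is valid but less precise than adjusting for the pre-treatment scan already collected

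*Protocol article*

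**What the plan says.** The first objective (Objectives) is to "investigate the influence of opposing EA treatment on the brain activities of patients after unilateral TKA compared with that of sham opposing EA treatment". Under MRI data acquisition each patient has two scans: "the first scan will be performed before the first intervention after surgery, and the second after all interventions are completed". They are called scan 1 and scan 2 below.

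The fMRI paragraph of Statistical analysis names one test for group differences in the three measures (amplitude of low-frequency fluctuation, regional homogeneity, functional connectivity): "A two-sample *t*-test will be used to evaluate intra- and inter-group differences to analyze possible brain responses". It mentions change between scans only for a different purpose: "a correlation analysis will be conducted to investigate the changes in fMRI image data and the corresponding clinical data in each group".

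The preceding paragraph says that "a generalized linear mixed model will be used to compare the repeated measurement data". That sentence is one of four analyses listed for the clinical data in SPSS, whereas the fMRI data are analysed in SPM12. The covariates regressed out in the fMRI preprocessing (cerebrospinal fluid signal and head-motion parameters) are noise terms within a scan, not an adjustment for scan 1.

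**The concern.** A two-sample t-test compares two group means and has no place for a covariate. Scan 1 is measured before treatment on the same patient with the same sequence, so it is a natural predictor of scan 2. If the test is run on scan 2 alone, that information is unused. If it is run on scan 2 minus scan 1, scan 1 is used, but with its coefficient fixed at 1 instead of estimated from the data.

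The comparison with sham on brain activity is the first objective, and the Sample size section justifies the number of patients by neuroimaging needs. What is at stake is the precision of that contrast in a trial of 40 patients per arm before losses.

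**Working it through.** **Inputs from the protocol article**
- Planned size: 40 per group, 1:1 allocation (Sample size; Randomization and blinding).
- Minimum: "the current study design requires at least 20 participants in each group".
- Losses: "considering a 20% drop-out rate during the trial and the possibility of head movement artifact". The head-movement loss is not quantified.
- Significance level: "The statistical significance will be set to two-sided *p* < 0.05". It is stated in the clinical paragraph and used here for a single test.

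**Inputs assumed**
- Scan-to-scan correlation rho: not given in the documents; 0.3, 0.5 and 0.7 are used, with values outside that range shown as well.
- Equal variance at scans 1 and 2.

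**The plan's own figure.** The plan gives no effect size, standard deviation or power for the fMRI comparison, so there is no power figure to reproduce. Drop-out alone takes 20 per group to 20/(1 − 0.20) = 25. The remaining step to 40 rests on the unquantified head-movement loss, so 40 can be neither reproduced nor called wrong. The power check uses 40 × (1 − 0.20) = 32 per group.

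**Step 1: relative variance of the group difference** (scan 2 alone = 1)
- t-test on change: 2(1 − rho)
- ANCOVA on scan 1: 1 − rho²
- ANCOVA against change: (1 − rho²)/[2(1 − rho)] = (1 + rho)/2

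| rho | Scan 2 alone | Change | ANCOVA | ANCOVA/change |
|---|---|---|---|---|
| 0.3 | 1 | 1.40 | 0.91 | 0.65 |
| 0.5 | 1 | 1.00 | 0.75 | 0.75 |
| 0.7 | 1 | 0.60 | 0.51 | 0.85 |

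So ANCOVA cuts the variance by 9%, 25% and 49% against scan 2 alone, and by 35%, 25% and 15% against change. A simulation with 4,000 runs at 32 per arm gave 1.00/1.39/0.92, 0.97/1.00/0.75 and 0.95/0.59/0.50 for scan 2 alone/change/ANCOVA, in agreement.

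**Step 2: power.** Noncentral t, 32 per arm, two-sided 0.05, with 62 degrees of freedom for the t-test and 61 for ANCOVA. The standardised effect giving the t-test 80% power is 0.71. It is then divided by √(1 − rho²) for the comparison with scan 2 alone, or by √[(1 + rho)/2] for the comparison with change. The two columns start from different effects, because each sets its own t-test at 80%.

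| rho | From 80% on scan 2 alone | From 80% on change |
|---|---|---|
| 0.1 | 80.4% | 96.5% |
| 0.2 | 81.6% | 95.1% |
| 0.3 | 83.5% | 93.5% |
| 0.5 | 89.9% | 89.9% |
| 0.7 | 97.5% | 85.9% |
| 0.8 | 99.7% | 83.9% |
| 0.9 | over 99.9% | 82.0% |

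The results are nearly the same with 20 or 40 per arm. At the stricter two-sided level of 0.001, with rho 0.5, an effect with 50% power on either t-test would have 69% with ANCOVA.

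**Step 3: the same gain in patients.** To match the variance of ANCOVA with 32 per arm:
- A t-test on scan 2 alone needs 32/(1 − rho²), or about 35, 43 and 63 per arm at rho 0.3, 0.5 and 0.7.
- A t-test on change needs 32 × 2/(1 + rho), or about 49, 43 and 38 per arm.

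**The case against.** **The plan may intend a change score.** The fMRI paragraph speaks of brain responses, the Sample size section links both scans to the contrast between acupuncture and sham, and changes in the images must be computed anyway for the correlation analysis. This stands: a reader might infer that scan 1 is ignored, but the text does not settle that. It narrows the point without removing it, since ANCOVA is also more precise than a change score for any rho below 1, apart from one degree of freedom.

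**The named test is not biased.** This also stands. A reader might infer that a difference between arms at scan 1 would be taken for an effect of opposing EA, or that a change score leaves regression to the mean uncorrected. In a randomised comparison, regression to the mean acts equally on both arms in expectation, and the error rate of the t-test already allows for chance imbalance. Either worry applies only conditionally, to an imbalance that happens to occur in the realised sample.

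**The size is not established.** The documents give no rho, and it will differ between voxels, regions and the three measures. The power figures describe one test and do not carry over directly to image-wide inference. All of this stands, and the figures should be read as an illustration.

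**The detail may sit in a fuller plan.** Partly right: the input to the test and any covariates could be specified there. But the article does name the test, and that test cannot hold a covariate.

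**The trial has enough patients by its own standard.** The plan asks for 20 per group, and 32 exceeds that. The primary clinical outcome is the pressure pain threshold. This limits the severity, but it does not justify giving up precision on the first objective when the data are already being collected.

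**Conclusion.** The point holds as one of efficiency. The protocol article fixes an unadjusted two-sample t-test for the between-group brain-activity comparison and leaves its input unstated. Both possible inputs give a valid test, and both are less precise than adjustment for scan 1 when rho lies between 0 and 1. Over the assumed range of 0.3 to 0.7 the gain from a starting power of 80% is about 4 to 18 percentage points against scan 2 alone and about 14 to 6 points against a change score. It shrinks to almost nothing for rho near 0 in the first case and near 1 in the second. These figures assume equal variances at the two scans, 32 patients per arm and a single test at two-sided 0.05. The change should be made because it is cheap, not because the planned test would mislead.

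**What to change.** In the fMRI paragraph of Statistical analysis, replace the inter-group t-test with wording such as: The comparison of opposing EA with sham for amplitude of low-frequency fluctuation, regional homogeneity and functional connectivity at the second scan will use a linear model with group as factor and the same patient's first-scan value at the same voxel, region or connection as covariate; the adjusted group difference addresses the first objective.

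This also settles whether the contrast uses scan 2 or the change. It should be fixed before any unblinded analysis.

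The cost is one sentence, one degree of freedom, and a short script or a toolbox that accepts voxel-wise covariates. No further scans, patients or staff are needed.

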#### Scheme of standard analgesic use

Within 48 h after TKA, participants will use a patient-controlled analgesia pump. Fentanyl (Yichang Renfu Pharmaceutical Co., Ltd., Yichang, China) will be used as an analgesic drug at a continuous infusion rate of 0.25 μg/kg/h, a bolus dose of 0.15 μg/kg, and a 10-min lockout time. In addition, all participants will begin oral administration of celecoxib capsules (Pfizer Pharmaceutical Co., Ltd., New York, USA), at a dosage of 200 mg once daily, 72 h after operation.

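### The fMRI plan names a two-sample t-test for within-group change, although each patient is scanned twice and those data are paired

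*Protocol article*

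**What the plan says.** The imaging paragraph of Statistical analysis names one test for two different comparisons: "A two-sample *t*-test will be used to evaluate intra- and inter-group differences to analyze possible brain responses". A correlation analysis of imaging changes with clinical data follows in the same sentence.

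MRI data acquisition fixes the scans per patient: "the first scan will be performed before the first intervention after surgery, and the second after all interventions are completed". The Sample size section agrees: "Each group will undergo two MRI scans to investigate the different central responses between contralateral acupuncture and sham acupuncture after right TKA".

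Under Objectives, the first aim is the effect of opposing electroacupuncture (EA) on brain activity "compared with that of sham opposing EA treatment". The second is to "analyze the possible correlations between the changes in cerebral activity and the improvement of clinical variables in each group".

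One method for repeated data is named: "Finally, a generalized linear mixed model will be used to compare the repeated measurement data". It is the last of four items in the paragraph on clinical data, which are analysed in SPSS. The imaging data have their own paragraph, their own software (SPM12) and their own named test.

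**The concern.** With two scans per patient, the intra-group comparison is scan 1 against scan 2 in the same people. A two-sample t-test assumes that the two sets of values come from different people. It therefore uses a standard error that leaves out the within-patient correlation.

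The article states this test explicitly, so this is not a detail left to a fuller document. No paired test or within-subject model is named for the scans. Followed literally, the rule would apply to every within-group map of low-frequency amplitude, regional homogeneity and functional connectivity. In a mechanism study those maps are supporting evidence that readers will look at.

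**Working it through.** **Inputs from the protocol article**
- Test for intra-group imaging differences: two-sample t-test (Statistical analysis).
- Scans per patient: two (MRI data acquisition; Sample size). The abstract can be read as listing three scan times; the data are paired either way.
- Patients: 40 per group, 20% drop-out, minimum 20 per group (Sample size). After drop-out, 40 × 0.80 = 32. Further loss to head movement is foreseen but not quantified, so n = 20 is shown as well.
- Significance level: two-sided 0.05. It is stated with the clinical analyses and used here for illustration.

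**Assumptions, because the article gives no figures**
- Correlation rho between a patient's two scans: 0.3, 0.5 and 0.7.
- True within-group change: 0.5 SD.
- Equal variance at both scans, normal data.

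The plan states no number on this point, so there is none to reproduce.

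**Standard error of the mean change**
- Targeted by the two-sample test: sqrt(2·SD²/n).
- Correct for paired data: sqrt(2·SD²·(1 − rho)/n).
- Ratio: 1/sqrt(1 − rho), whatever n is.

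With SD = 1 and n = 32, the two-sample value is sqrt(2/32) = 0.250.

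| rho | Correct SE | Ratio |
|---|---|---|
| 0.3 | sqrt(1.4/32) = 0.209 | 1.20 |
| 0.5 | sqrt(1.0/32) = 0.177 | 1.41 |
| 0.7 | sqrt(0.6/32) = 0.137 | 1.83 |

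**Effect on a single test, n = 32** (simulation, at least 40,000 replicates per cell)

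| rho | Type I error, two-sample | Type I error, paired | Power, two-sample | Power, paired |
|---|---|---|---|---|
| 0.3 | about 2% | about 5% | about 51% | about 64% |
| 0.5 | about 0.7% | about 5% | about 51% | about 78% |
| 0.7 | below 0.1% | about 5% | about 51% | about 94% |

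A hand check explains the flat 51%. The two-sample statistic centres on 0.5/0.250 = 2.0, which is about its critical value, so it rejects roughly half the time whatever rho is. The paired statistic centres on 0.5/0.209 = 2.4, 0.5/0.177 = 2.8 and 0.5/0.137 = 3.6.

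**Other cases**
- At n = 20, power is about 31% against 44% (rho 0.3), 29% against 57% (0.5) and 24% against 78% (0.7).
- At rho = 0 the type I error is about 5% for both tests.
- At rho = −0.2 the two-sample test becomes mildly anti-conservative, at about 7%. A negative correlation between repeat scans of one person is not expected.

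**Inter-group side.** A two-sample t-test on scan 2 minus scan 1, compared between arms, keeps its level: simulated type I error is 4.9% to 5.1% at n = 20 and n = 40.

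**The case against.** The strongest defence is that the damage is limited. The first objective is a contrast with sham between independent patients, where a two-sample t-test is valid. The second is served by a correlation analysis. What remains wrong is a set of supporting within-group maps, and there the error makes the test too cautious. All of this stands, and it sets the scope of the point.

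The wording may also simply be loose: the clinical paragraph specifies independent samples for its t-tests, and the imaging paragraph does not. That is possible, but a two-sample t-test is ordinarily the unpaired one, so the sentence still needs correcting.

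A reader might infer more than the article supports:
- *The main objective is tested invalidly.* It is not, for the reason just given.
- *The inter-group test ignores scan 1, or the EA effect will be read off two separate within-group maps.* The article says neither. It does not state which image enters the inter-group test, and a test on difference maps fits its text. A comparison at scan 2 alone would also be a valid randomised contrast, though it leaves scan 1 unused.
- *Within-group change will be credited to EA, although "all participants will begin oral administration of celecoxib capsules" at 72 h, when EA also starts.* The article makes no such claim. Celecoxib and surgical recovery are common to both arms, and the sham comparison deals with them.
- *The wrong test will produce false brain findings.* With positive correlation it does the opposite.

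**Conclusion.** The point holds in this limited form. The test named for intra-group imaging differences does not fit paired scans, and nothing else in the article corrects it for the imaging data. The wrong standard errors are confined to the within-group results.

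The direction rests on rho being positive, and the size on the assumed rho values; the power figures also rest on the assumed 0.5 SD change and on 32 analysable patients per arm. All rates are for a single test at 0.05 and are not error rates for a whole-brain map. That the test is wrong for paired data depends on none of these assumptions. It should be corrected before the imaging data are analysed.

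**What to change.** Replace the sentence on the two-sample t-test with:

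> Intra-group changes between the two scans will be tested with a paired t-test (one-sample t-test on difference maps). Inter-group differences will be tested with a two-sample t-test on each patient's scan 2 minus scan 1 map (group × time).

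The correlation analysis can stay as it is. The second sentence also settles which image enters the comparison with sham. The cost is one sentence of analysis text; SPM12 provides both models, and no new data or scans are needed.
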